### 8.4.1 Double Reporting of Reactogenicity Findings/Complaints and Findings of Influenza as Adverse Events:

As per sections 8.1, and 8.2 above, findings and/or complaints specifically captured by the Immediate Complaints Questionnaire (Appendix E), the Brief Examination Worksheet (Appendix C), or the Memory Aid (Appendix D) should NOT, in general, be additionally recorded as AEs if they occur within seven (7) days of a test article dose.

The rationale for not in general doubly-reporting reactogenicity events as AEs is as follows. The specified range of reactogenicity complaints and findings in Appendices C, D, and E are those reasonably expected (theoretically and by experience) to be associated with a nasal vaccine. They are collected, *presumed to be drug-related*, analyzed, and reported to investigators and regulatory authorities in detail as expected vaccine reactions. Separation of these numerically very frequent, but minor and anticipated, vaccine reactions from other classes of adverse events prevents the obscuration of other potentially important, but less common, types of events in the statistical analysis of AEs.

There are *three exceptions* to the rule regarding double reporting:

1. Any of these findings or complaints which fulfills the definition of “serious adverse event” (see section 8.5) should be recorded as an AE (and reported as per section 8.5),
2. Any of these findings or complaints that persists beyond seven (7) days after a test article dose should be recorded as an AE,
3. Any of these findings or complaints which the investigator *unequivocally* categorizes, based on strong clinical evidence, as unrelated to the test article should be recorded as an AE. In this case the investigator *must* assign a causality of “probably not related” (not “unknown”) and record a clear rationale in source documents.

If a reactogenicity finding or complaint is also recorded as an AE, site personnel should take care to record a verbatim AE identical to the wording of the reactogenicity finding/complaint, and also an AE start date identical to the onset

date implied by the reactogenicity case report forms. The sponsor will report these events as both reactogenicity and AE findings, but will be able to link the two reports in the database for discussion and analysis purposes.

As per section 8.3 above, the symptoms and physical findings of influenza captured by the Influenza Symptom Diary Card (Appendix F) and the Challenge Physical Examination Worksheet (Appendix G) will also not in general be additionally recorded as AEs. The sole exception to this rule will be that symptoms or physical findings of influenza which fulfill, singly or collectively, the definition of “serious” as per section 8.5 will be recorded as serious AEs and be reported in accordance with section 8.5.

# 9.0 Analysis Plan:

This is a phase II, four-group, placebo-controlled, randomized clinical trial. Approximately 28 subjects will be treated in each group. Volunteers will either receive two 15 µg treatments separated by two weeks, one 30 µg and one placebo treatment separated by two weeks, two 30 µg treatments separated by two weeks, or two placebo treatments separated by two weeks. In the immediate post-treatment period, outcomes are pre-specified local and systemic reactions, general adverse event rates, and immune responses assessed by antibody measurements.

Forty-one (± 3) days after the first treatment, subjects who remain eligible are challenged and then followed for an additional week regarding evidence of illness (by several alternative definitions), and also concerning virologic outcomes.

All analyses will be done with SAS, version 8.2 or later, primarily PROC UNIVARIATE, FREQ, LOGISTIC (for logistic regression with challenge data), and GENMOD (SAS PROC GENMOD implements the repeated measures regression model of Zeger and Liang [48].) Chi-square tests in PROC FREQ are exact. In this phase II trial which will not be used to provide definitive evidence of efficacy or safety, p-values of 0.05 or less for two-sided statistical tests will be considered significant and multiple comparison corrections will not be used (although the rather large number of significance tests – at least as regards safety -makes it likely that the type I error rate will be somewhat elevated.

Simple methods will be used to impute missing data. For binary outcomes, such as the presence/absence of an adverse event, alternative imputations will assume the event did, and did not, occur and the results of these contrary assumptions will be compared. For continuous outcomes, such as antibody titers, last-value-carried-forward will be used except that two consecutive missing values will not be imputed.

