### 7.2.6 Specific Immune Response Assays :

 Serum will be obtained for influenza-specific special serologies (serum hemagglutination-inhibition titers) at the First Screening Visit (A/Panama/2007/99 only), at the Immunization Phase Day 0 visit (all three strains tested for this and subsequent samples), and on Immunization Phase Day**,** 28 (± 3), Challenge Phase Day 0, and Challenge Phase Day 20 - 30.Should hemagglutination-inhibition prove unworkable for the influenza B virus component, single radial hemolysis assay may be utilized.

- Nasal washes for influenza-specific secretory IgA by ELISA will be obtained at the Second Screening Visit (all three strains tested for this and subsequent samples), and on Immunization Phase Day**,** 28 (± 3), Challenge Phase Day 0, and Challenge Phase Day 20 - 30.
- Whole blood will be obtained for *in vitro* cytokine stimulation studies on Immunization Phase Day 0 and Immunization Phase Day28 (± 3).

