## 9.1 Immunogenicity:

Immunogenicity measures will include serum hemagglutination-inhibiting (HAI) antibody titers specific for the three virus strains included in the vaccine, and levels of secretory IgA (sIgA) specific for these viruses measured in nasal wash fluids. Antibody levels in nasal wash specimens will be assayed by kinetic ELISA and normalized on total content of sIgA. For the HAI titers, analyses will concern geometric mean titers (GMT), proportions of subjects with titer ≥ 40, and proportions with  four-fold increase over baseline. For specific sIgA levels, analyses will concern geometric means and fold-rise from baseline.

HAI GMTs and geometric mean nasal specific sIgA levels will be accompanied by 95%, Student’s t-based confidence intervals. Between active-to-placebo and active-to-active cross-over groups, titers/antibody levels will be compared on day 28 by t-tests on log10 (titer). Within the groups, paired tests will be used (Student’s t and Wilcoxon signed rank).Fold-rises may be examined with and without covariate-adjustment for previous titers. Without such adjustment, there are two binary fold-rise outcomes, and these are compared within and between groups by chi-square and stratified chi-square tests. (In the latter case, 2 x 2 tables of treatment by outcome are stratified by previous titers.) With covariate adjustment, the fold-rise outcome is the log10-ratio of early and later titers. Adjustment after the first treatment is for baseline titer and after the second treatment is for both baseline titer and titer after the first treatment. This facilitates contemporaneous between-group comparisons of placebo and active after both periods 1 and 2.

9.2 Safety:

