- A  4-fold increase in serum A/Panama/2007/99 HAI antibody titer between day 39 ( 3) and the final follow-up visit, and absent clinical disease suggesting influenza between discharge from the isolation unit and the final follow-up visit.

9.3.7 Laboratory-confirmed Influenza Illness:

A subject will be deemed to have laboratory-confirmed influenza illness if he/she meets the definitions for BOTH of:

- Influenza infection, and
- Illness (Any).

9.3.8 Analysis:

9.3.8.1 Power Considerations:

The analysis will consider both binary outcomes (e.g., illness vs. no illness; virus shedding vs. no virus shedding, etc.) and continuous outcomes (e.g., treatment group mean temperatures, tissue counts, peak viral shedding and shedding AUC, etc.). The variability, and potential magnitudes of the differences in the latter are *a priori* unknown. However, the virus challenge inoculum will be selected to yield *approximately* 50 - 60%, based on past experience, of the binary outcome “any illness.” (Closer control of this rate is difficult to ensure.) Assuming that a minimal efficacy level of 70% (where efficacy = [rate controls -ratetreated ] x 100 / rate controls) is of interest to justify further development of a given dose or formulation, it is possible to calculate that a group size of 28 will yield ≥ 0.80 power to detect a ≥ 70% reduction in the rate of the binary outcome “any illness.”

9.3.8.2 Analyses:

The analysis concerns between-group comparisons of the four cross-over groups regarding clinical and immunologic binary outcomes. Alternative definitions provide six binary clinical outcomes (fever, upper respiratory illness, lower respiratory illness, systemic illness, illness [any], and illness + infection) that can be compared between groups by chi-square tests. More flexible analyses use logistic regression (SAS PROC LOGISTIC) with the presence or absence of influenza, separately for each definition, as the outcome. Covariates are cross-over study group, age, gender, race, and, for some models, titers after vaccinations 1 and 2.

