Additional secondary analyses will be based on tissue counts (and weights, if feasible) as a marker of illness severity, and on virus shedding assessed by two methods: peak and a time-weighted average calculated as a trapezoidal-rule AUC. For both peak and AUC, viral shedding is in units of log10 (titer). These continuous data will be compared between cross-over groups by Student’s t-tests and Wilcoxon tests and, in a more flexible analysis, by linear model adjusted for the demographic and clinical covariates cited above.

Finally, the three binary measures of influenza and the two viral load estimates (peak titer and AUC) will be assessed relative to the two immunologic measures, HAI reciprocal titer and nasal secretory IgA. For the binary measures, mean viral load (for each measure) is compared by t-tests between those with and without influenza (for each definition). For the two immunologic measures, the test of association with viral load will be based on Pearson correlations of log-titers.

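### Last-value-carried-forward for antibody titers fills an isolated missing Day 28 sample with a pre-vaccination value, and a missing final HAI with the pre-challenge value

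*Protocol*

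**What the plan says.** Protocol section 9.0 sets two missing-data rules in one paragraph. For continuous data: "For continuous outcomes, such as antibody titers, last-value-carried-forward will be used except that two consecutive missing values will not be imputed". For binary data: "For binary outcomes, such as the presence/absence of an adverse event, alternative imputations will assume the event did, and did not, occur", after which the two sets of results are compared.

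Section 7.2.6 fixes the specimens. Serum HAI is taken "at the Immunization Phase Day 0 visit (all three strains tested for this and subsequent samples"), then at Day 28, "Challenge Phase Day 0, and Challenge Phase Day 20 - 30". An earlier screening serum is tested for A/Panama only. For the mucosal response, "Nasal washes for influenza-specific secretory IgA by ELISA will be obtained at the Second Screening Visit", and then at the same three later visits.

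Section 9.1 places the between-group comparison at Day 28: "titers/antibody levels will be compared on day 28 by t-tests on log10 (titer"). It also analyses the proportions with a titer of at least 40 and with a four-fold rise, and the log-ratio fold-rise.

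Section 9.3.6 counts a subject as infected on any one of three findings: virus in nasal wash, virus in throat swab, or a "4-fold increase in serum A/Panama/2007/99 HAI antibody titer between day 39" and the final visit. Section 9.3.7 then requires infection together with illness for laboratory-confirmed influenza illness.

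**The concern.** Carrying a value forward is harmless only if nothing relevant happened between the two samples. Here the intervals that matter contain the very event whose effect is being measured: vaccination lies between baseline and Day 28, and challenge lies between day 39 and the final visit. A value carried across either interval asserts that there was no response.

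At Day 28 the error has a direction. Placebo titers are expected to stay flat before challenge, so filling with baseline changes little there. In an active group the same step lowers the geometric mean titer, the geometric mean sIgA and the log-ratio fold-rise. The contrast with placebo shrinks.

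At the final visit, the carried day 39 value is also the denominator of the serological criterion. That criterion matters in this trial because section 1.0 reports that culture was insensitive for this strain in the preceding challenge study.

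**Working it through.** No figure in the protocol depends on this rule, so there is nothing to reproduce. The check applies the rule to the schedule and then sizes the effect.

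**Step 1: what is carried forward**

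| Missing sample (others present) | Value carried in | Consequence |
|---|---|---|
| Day 28 HAI | Day 0, pre-vaccination | fold-rise = 1 |
| Day 28 sIgA | second screening visit, pre-vaccination | fold-rise = 1 |
| Day 39 HAI or sIgA | Day 28, post-vaccination | not this problem |
| Final HAI | day 39, pre-challenge | ratio = 1, so no four-fold rise |
| Day 28 and day 39 together | none (two consecutive) | left out |

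The first and last rows together are perverse. A subject with a high observed day 39 titer who missed only Day 28 enters the Day 28 comparison at the pre-vaccination level. A subject with neither sample is left out. The subject who supplied more information is represented less accurately.

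**Step 2: inputs for the size**

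- Group size n = 28 (section 9.0).
- True HAI response r = 70%, taken from the preceding challenge study described in section 1.0.
- True geometric mean rise g = 4. This is an assumption; the protocol gives no HAI figure of this kind.
- Isolated missing Day 28 sera m = 1, 2 or 3, missing independently of response. This is also an assumption; the protocol gives no missing rate.

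**Step 3: effect at Day 28**

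If response is derived from the imputed titer, the expected responder rate is r × (n − m)/n. The geometric mean rise is g^((n − m)/n), because each carried value contributes a log-rise of zero. Under the both-extremes rule, the rate would run from r(n − m)/n to r(n − m)/n + m/n.

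| m | Responders, carried forward | Responders, both extremes | Geometric mean rise, carried forward |
|---|---|---|---|
| 1 | 0.70 × 27/28 = 67.5% | 67.5% to 71.1% | 4^(27/28) = 3.81 |
| 2 | 0.70 × 26/28 = 65.0% | 65.0% to 72.1% | 4^(26/28) = 3.62 |
| 3 | 0.70 × 25/28 = 62.5% | 62.5% to 73.2% | 4^(25/28) = 3.45 (3.448, or 3.4 to one decimal) |

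Analysing observed values only, under the same assumption, leaves the expected results at 70% and 4-fold.

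Expressed as a share missing, 5%, 10% and 20% give 66.5%, 63% and 56% responders, and rises of 3.73, 3.48 and 3.03.

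**Step 4: effect at the final visit**

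Take the serological limb alone, with assumed true rates of 60% on placebo and 18% on vaccine, a reduction of 1 − 18/60 = 70%. Again assume the limb is derived from the imputed titer.

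- Equal missingness, 20% in each arm: 1 − 14.4/48 = 70%, unchanged.
- 20% missing on placebo only: 1 − 18/48 = 62.5%.
- 20% missing on vaccine only: 1 − 14.4/60 = 76%.

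The serological rates themselves fall in every case. The relative reduction moves only if missingness differs between arms.

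**The case against.** The best defence is that the protocol may already handle the binary endpoints properly. Section 9.1 calls the fold-rise outcomes binary, section 9.3.8.2 speaks of immunologic binary outcomes, and the both-extremes rule stands in the same paragraph as the carry-forward rule. On that reading a missing four-fold rise or serological infection is imputed both ways, and nobody is fixed as a non-responder. This stands as a real ambiguity. It does not reach the geometric means or the log-ratio fold-rise, which are continuous, and antibody titers are the rule's own named example.

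The exception also does useful work. A subject who leaves before Day 28 misses Day 28 and day 39 together, so neither is imputed, and section 7.4 asks for a full final evaluation even after withdrawal. What remains is the isolated missed Day 28 sample and the missed final visit. The number of such samples may be small.

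A reader might infer more than the documents support:

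- **Daily shedding.** Challenge is given on Challenge Phase Day 2 and the post-challenge samples run from Day 3 to Day 9 (sections 7.1.12 and 7.2.7). A value carried from Day 3 onward therefore follows the challenge, and the argument above does not extend to shedding.
- **Confidence intervals.** They are not necessarily too narrow. Putting baseline values into a responding arm adds spread. Assume 3 of 28 carried, a log10 rise of 0.602 and a carried-value SD of 0.1. With a Day 28 SD of 0.3, the standard error is about 0.064, against 0.3/√25 = 0.060 on observed data. At SD 0.4 the two are about equal; at 0.5 the imputed one is slightly smaller.
- **Infection.** It is not undercounted wherever the final serum is missing. Nasal wash or throat swab detection is enough, so only subjects negative on all virology are exposed.
- **Titer of at least 40.** The entry limit of 10 in section 4.2 covers A/Panama only. For the other two strains a carried Day 0 titer may already meet this threshold.

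**Conclusion.** The rule is wrong as written for antibody titers at two visits. At Day 28 an isolated missing HAI or sIgA value is replaced by a pre-vaccination one, and continuous active-arm results move toward placebo. This holds on either reading of the binary rule. At the final visit the serological limb of infection is negative by construction only if it is derived from the imputed titer, which the protocol leaves open.

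With few missing samples the effect is modest: for one missing serum in 28, 70% becomes 67.5% and a 4-fold rise becomes 3.8. It grows with missingness. These sizes rest on an assumed number of missing samples and missingness unrelated to response. The responder figure also assumes derivation from the imputed titer, and the fold-rise figure rests on the assumed 4-fold HAI rise. The direction at Day 28 rests only on vaccinees responding and placebo staying flat. The change should be made, but the point does not threaten the design.

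**What to change.** In section 9.0, delete last-value-carried-forward for antibody titers at Day 28 and the final visit. Analyse observed log10 titers, or fit a likelihood-based repeated-measures model that includes baseline; the model uses an observed day 39 titer when Day 28 is missing. Either choice keeps the Day 28 comparison of section 9.1.

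Add one sentence stating that four-fold rise, titer of at least 40 and serological infection, when the titer needed is missing, go through the both-extremes rule already in section 9.0. Add that a subject positive by nasal wash or throat swab counts as infected whatever the serology.

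The cost is analysis wording and minor programming. No visit, specimen or sample size changes.

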## 9.1 Immunogenicity:

Immunogenicity measures will include serum hemagglutination-inhibiting (HAI) antibody titers specific for the three virus strains included in the vaccine, and levels of secretory IgA (sIgA) specific for these viruses measured in nasal wash fluids. Antibody levels in nasal wash specimens will be assayed by kinetic ELISA and normalized on total content of sIgA. For the HAI titers, analyses will concern geometric mean titers (GMT), proportions of subjects with titer ≥ 40, and proportions with  four-fold increase over baseline. For specific sIgA levels, analyses will concern geometric means and fold-rise from baseline.

HAI GMTs and geometric mean nasal specific sIgA levels will be accompanied by 95%, Student’s t-based confidence intervals. Between active-to-placebo and active-to-active cross-over groups, titers/antibody levels will be compared on day 28 by t-tests on log10 (titer). Within the groups, paired tests will be used (Student’s t and Wilcoxon signed rank).Fold-rises may be examined with and without covariate-adjustment for previous titers. Without such adjustment, there are two binary fold-rise outcomes, and these are compared within and between groups by chi-square and stratified chi-square tests. (In the latter case, 2 x 2 tables of treatment by outcome are stratified by previous titers.) With covariate adjustment, the fold-rise outcome is the log10-ratio of early and later titers. Adjustment after the first treatment is for baseline titer and after the second treatment is for both baseline titer and titer after the first treatment. This facilitates contemporaneous between-group comparisons of placebo and active after both periods 1 and 2.

9.2 Safety:

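### The only committed between-group test of antibody levels ignores the baseline values the trial collects, and the optional adjusted analysis cannot be run after the second dose as written

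*Protocol*

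**What the plan says.** The Synopsis lists the magnitude of serum and mucosal immune responses as the second objective. For active-to-placebo and active-to-active contrasts, section 9.1 states that "titers/antibody levels will be compared on day 28 by t-tests on log10 (titer"). The Synopsis (Statistical Methods) names the same test.

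Baseline values are scheduled for every subject. Section 7.2.6 places serum HAI "at the Immunization Phase Day 0 visit (all three strains tested for this and subsequent samples"), and for the mucosal measure "Nasal washes for influenza-specific secretory IgA by ELISA will be obtained at the Second Screening Visit (all three strains tested for this and subsequent samples").

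Section 9.1 then describes analyses that do use baseline:

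- "Fold-rises may be examined with and without covariate-adjustment for previous titers".
- For the unadjusted binary fold-rise outcomes, chi-square tests, including a version in which "2 x 2 tables of treatment by outcome are stratified by previous titers".
- For the adjusted version, "With covariate adjustment, the fold-rise outcome is the log10-ratio of early and later titers".
- The covariates: "Adjustment after the first treatment is for baseline titer and after the second treatment is for both baseline titer and titer after the first treatment".
- The stated purpose: "This facilitates contemporaneous between-group comparisons of placebo and active after both periods 1 and 2".

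**The concern.** Section 4.2 restricts entry on one baseline antibody measure only, A/Panama HAI at 10 or below. Baseline H1N1 HAI, influenza B HAI and all three nasal sIgA levels are unrestricted. Whatever part of a subject's Day 28 level is predictable from baseline stays in the error term of the t-test.

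This matters most for the active-to-active contrasts. Groups have about 28 subjects (section 9.0). Section 1.0 reports sIgA rises of 3- to 4-fold after two-dose regimens and 1.8- to 3-fold after one dose, so the expected difference between one and two doses is modest. Those figures do not address 15 µg twice against 30 µg twice.

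The adjusted analysis would normally answer this concern, but it is only permitted ('may') where the t-test is promised ('will'), and its specification does not match the sampling schedule.

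**Working it through.** **1. Can the adjusted analysis be run as written?**

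| What section 9.1 needs | What is scheduled (section 7.2.6; Appendix B, Table B.1) |
|---|---|
| Baseline titre | HAI on Day 0; sIgA at second screening |
| Titre after the first treatment (as outcome for period 1, as covariate for period 2) | None. The Day 14 visit (section 7.1.6) takes no blood for antibody and no nasal wash |
| Titre after the second treatment | HAI and sIgA on Day 28 |

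The period-1 form has no outcome sample, and the period-2 form lacks one of its two covariates. If the missing titre existed, it would itself be a response to randomised treatment. Conditioning on it would remove part of the vaccine effect. Group B against Group D shows this most clearly, because both receive placebo as the second dose (section 5.1.1).

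**2. What if baseline is the only covariate?**

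Let y0 and y28 be the log10 levels. The log10-ratio model is

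y28 − y0 = a + τ·arm + g·y0 + e,

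which rearranges to

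y28 = a + τ·arm + (1 + g)·y0 + e.

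The treatment effect τ and its standard error are identical. The log10-ratio analysis restricted to baseline is therefore the same as an ANCOVA of Day 28 level on arm and baseline.

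**3. How much precision is at stake?**

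The protocol states no power, SD or target difference for immunogenicity, so there is no figure to reproduce. Inputs: n = 28 per arm (section 9.0); two-sided alpha 0.05 (section 9.0); correlation rho between baseline and Day 28 assumed, range 0.1 to 0.7.

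Difference detectable with 80% power without adjustment (normal approximation):

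d0 = (1.960 + 0.842) × √(2/28) = 2.802 × 0.2673 = 0.749 SD.

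Adjustment multiplies the SD by √(1 − rho²). Power at d0 is then Φ(2.802/√(1 − rho²) − 1.960). The equivalent unadjusted group size is 28/(1 − rho²).

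| rho (assumed) | 1 − rho² | Detectable difference (SD) | Power at d0 | Equivalent n per arm |
|---|---|---|---|---|
| 0 (no gain) | 1.00 | 0.749 | 80.0% | 28.0 |
| 0.1 | 0.99 | 0.745 | 80.4% | 28.3 |
| 0.3 | 0.91 | 0.714 | 83.6% | 30.8 |
| 0.5 | 0.75 | 0.648 | 89.9% | 37.3 |
| 0.7 | 0.51 | 0.535 | 97.5% | 54.9 |

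A noncentral-t calculation, with one degree of freedom charged for the covariate and a starting difference of 0.762 SD, agrees: about 80% becomes 83.5%, 90% and 97.5% at rho 0.3, 0.5 and 0.7.

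**4. What this means for one dose against two**

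Assume equal baseline means and take the section 1.0 sIgA ranges.

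- Midpoints, 3.5- against 2.4-fold: log10(3.5/2.4) = 0.164. Power of 80% needs a Day 28 SD of at most 0.164/0.749 = 0.22 log10 unadjusted, or 0.164/0.648 = 0.25 adjusted at rho 0.5.
- Widest gap, 4- against 1.8-fold: log10(4/1.8) = 0.347. The limits are 0.347/0.749 = 0.46 unadjusted and 0.347/0.648 = 0.54 adjusted.
- Narrowest, 3- against 3-fold: no difference to detect.

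The protocol gives no SD against which to set these limits.

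**The case against.** The strongest reply is that section 9.1 already contains the remedy. The log10-ratio analysis with baseline as covariate is algebraically the proposed ANCOVA, and its stated purpose is a between-group comparison. Baseline also enters through the four-fold-rise proportions, the paired within-group tests and the stratified chi-square tests. A reader might therefore infer from the t-test alone that the plan leaves all baseline variation as noise. The documents do not support that reading.

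The objection does not dispose of the point. The adjusted analysis is optional, and its period-specific forms do not fit the sampling schedule. The stratified tests cover binary fold-rises, not geometric means. A baseline-only fit is feasible, but it is not what section 9.1 specifies after the second treatment.

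Other parts of the objection stand:

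- A reader might infer that the t-test is biased or invalid under chance baseline imbalance. It is not: allocation is randomised 1:1:1:1 (section 5.1.1), and the standard error already covers such imbalance.
- A reader might call the t-test the least efficient choice. That is not generally true. With equal variances, an unadjusted change score has relative variance 2(1 − rho), which exceeds 1 whenever rho is below 0.5.
- The gain rests on an assumed rho. The sIgA baseline may be taken up to 90 days before Day 0 (section 7.1.2), so up to 90 + 28 = 118 days before the nominal Day 28 sample, which could weaken the correlation.
- Section 9.0 says the trial will not give definitive evidence of efficacy or safety, and a statistical analysis plan that is not shown could settle which analysis is the main one.

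**Conclusion.** The point holds as one of precision and specification. The unadjusted Day 28 t-test is the only between-group test of continuous antibody levels that the protocol both commits to and can carry out as written. It is valid. The cost is avoidable loss of power, whose size the document cannot fix: about 4 points at rho 0.3, 10 at rho 0.5 and 17 to 18 at rho 0.7, from an assumed starting power of 80% at 28 per arm. At rho 0.1 it is under half a point. For A/Panama HAI, the challenge strain, the entry limit leaves little baseline spread and the gain should be small. A material gain is plausible for H1N1 HAI, B HAI and nasal sIgA, where baseline is unrestricted. The mismatch between the adjusted model and the sampling schedule needs correcting whatever rho proves to be.

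**What to change.** In section 9.1 and the Synopsis:

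1. Name as the main between-group analysis a linear model of log10 Day 28 level on treatment arm and the subject's log10 baseline for the same strain and assay (Day 0 HAI; second-screening sIgA). Report adjusted geometric mean ratios with 95% confidence intervals for the active-to-placebo and active-to-active contrasts.
2. Keep the unadjusted GMTs and geometric mean sIgA levels with their intervals, and the t-test, as supportive.
3. Delete the titre after the first treatment as a covariate, together with the reference to adjusted comparisons after period 1, for which no sample exists.

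The change needs no new sample or visit. It costs a revision of wording and one model degree of freedom per test.
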